### Data analysis

The primary analysis is to compare the rate of live births after at least 26 completed weeks of gestation between the combined use of prednisone, HCQ, and anticoagulant with the anticoagulant only. All data will be analyzed according to the intention-to-treat approach in which all randomized patients are included and supplemented by per-protocol analysis. For categorical data, frequencies and percentages will be presented. Continuous data will be presented as the mean and standard deviation or median and interquartile range. Comparison between groups will be performed using the independent sample *t* test, Pearson’s *χ*^2^ test, or Fisher’s exact test as appropriate. The primary outcome will be summarized as the proportion of live birth in each group. The absolute differences and relative risks with 95% confidence intervals will be described for the primary and secondary outcomes. The relative risks will be adjusted for age and number of previous miscarriages.

The trial has a single primary endpoint, i.e. rate of live births after at least 26 completed weeks of gestation between the combined use of prednisone, HCQ and anticoagulant with the anticoagulant only. All secondary comparisons, including comparisons to the third treatment arm (HCQ and anticoagulant) will be performed to further inform the primary endpoint and will be interpreted on this basis.

A sensitivity analysis using multiple imputations will assess the robustness of the results to variation in the missing data assumptions. Subgroup analysis will be conducted according to the number of previous miscarriages (2 or ≥ 3). Two-tailed significance tests will be performed at the 5% significance level, without adjustment for multiple testing.

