## Methods/design

### Study design

The ILIFE trial is a three-arm, multicenter, open-label, randomized controlled trial (RCT) to assess the efficacy of low-dose corticosteroids and HCQ combined with anticoagulation in treating UCTD women with recurrent pregnancy loss.

Patients will be enrolled at rheumatology outpatient clinics in six university-affiliated, tertiary hospitals in China, including Shanghai Renji Hospital, the First Affiliated Hospital of Anhui Medical University, China-Japan Union Hospital of Jilin University, the Affiliated Wuxi No.2 People’s Hospital of Nanjing Medical University, Jiangsu Province Hospital, and Xiangya Hospital of Central South University. The study design is presented in the flowchart in Fig. 1. Standard Protocol Items: Recommendations for Interventional Trials (SPIRIT) are provided as Additional file 1. This study was approved by institutional review boards (IRB) of study sites.

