### Randomization and blinding

The primary objective of this trial is to investigate the superiority of low-dose corticosteroids and HCQ combined with anticoagulation compared with anti-coagulant only in UCTD women with RSA. A third arm of using hydroxychloroquine combined with anticoagulant for a secondary comparison only. It is an open-label trial, but data analysts will be blinded. After obtaining the written informed consent, eligible patients will be randomized to one of the three treatment arms with a ratio of 1:1:1 stratified by site. Randomized numbers will be generated through SAS software at the trial methods center located in Shanghai Renji Hospital. A specially designed sealed opaque two-couplet random allocation envelope will be used for the randomization and allocation. The first couplet is to collect the enroll information and the second couplet is to show the allocation information. The content of the first couplet can be completely copied to the second couplet. Each time a new patient is enrolled in the study, a new envelope will be opened in order. Once the envelope is opened, it cannot be resealed.

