### Sample size

There is very limited evidence on the spontaneous pregnancy loss in pregnancies of women with UCTD and the reported risk rates for RSA varied substantially across studies. The live birth rate of a randomized trial enrolling 364 women with a history of unexplained recurrent miscarriage was 69.1% in the group receiving aspirin plus nadroparin [43]. In another cohort study of women with positive aPL, HCQ can improve the live birth rate from 57 to 67% [38]. A double-blind placebo randomized control trial involving 160 patients with unexplained recurrent miscarriage showed that the addition of prednisolone to heparin and aspirin might be beneficial, with 70.3% of women in the prednisolone group having successful pregnancy outcome versus 9.2% in the placebo group [30]. Data from 68 pregnancies in our department showed that the live birth rate was 97.1% in UCTD women with RSA treated by hydroxychloroquine plus low-dose prednisone combined with anticoagulation.

Our primary comparison is between the combined use of prednisone, HCQ, and anticoagulant with the anticoagulant only. Based on our pilot and limited published data, we hypothesize that the proportion of live birth rates with the treatment strategy using prednisone, HCQ, aspirin, and LMWH is 85% vs 70% for anticoagulant only. We need to enroll 363 women (121 in each group and for the third arm as well) to allow us to detect the difference in spontaneous pregnancy loss between the treatment groups with a power of 0.8 at a two-sided *P* value of 0.05. Since not all women would get pregnant during the trial, we planned to include about 426 participants (142 in each group) on the assumption of 90% of the pregnant rate within 1 year and 5% loss to follow-up [44].

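### Site is the only randomisation stratum but is left out of the analysis: a minor, nearly free efficiency gain is missed, with no inflation of type I error

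*Protocol article*

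**What the plan says.** Protocol article, Randomization and blinding: "eligible patients will be randomized to one of the three treatment arms with a ratio of 1:1:1 stratified by site". Study design gives the number of strata: "six university-affiliated, tertiary hospitals in China". No other stratification factor is named, and no block scheme is described.

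Protocol article, Data analysis, on testing: "Comparison between groups will be performed using the independent sample *t* test, Pearson’s *χ*^2^ test, or Fisher’s exact test as appropriate". None of these tests is stratified. On estimation: "The absolute differences and relative risks with 95% confidence intervals will be described for the primary and secondary outcomes", followed by "The relative risks will be adjusted for age and number of previous miscarriages". Site appears in that section neither as a stratum nor as a covariate.

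**The concern.** Stratified allocation removes chance imbalance between arms within each hospital. An analysis that ignores the hospital computes its standard error as if that imbalance could still occur, so between-hospital variation stays in the error term. Where hospitals differ in live-birth rate, the standard error is then larger than the true sampling variation, the test rejects too rarely under the null, and some power is lost. Age and number of previous miscarriages would remove this only as far as they explain the differences between hospitals.

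At stake is efficiency and agreement between design and analysis. There is no risk of a false claim of benefit.

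The point concerns what the article states, not what it omits. It gives an explicit list of tests and an explicit list of covariates, and the list does not match the design it describes.

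**Working it through.** **1. The plan's own figure.** The Sample size section assumes that live birth with "prednisone, HCQ, aspirin, and LMWH is 85% vs 70% for anticoagulant only", with power 0.8 at two-sided 0.05. With pooled variance and no continuity correction, mean rate 0.775:

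n = [1.960·√(2·0.775·0.225) + 0.842·√(0.85·0.15 + 0.70·0.30)]² / 0.15² = 120.5, so 121 per group.

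This matches "We need to enroll 363 women (121 in each group and for the third arm as well"). Power at 121 per group is 80.2%. The inflation also reproduces: 121/(0.90 × 0.95) = 141.5, so 142 per group.

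**2. Assumption needed.** The article gives no between-site variation. The SD of the site effects on the logit scale was therefore varied from 0 to 1.0. With the control rate averaging 70%, SD 0.5 means control rates of about 53% to 84% across six sites, and SD 1.0 about 38% to 93%.

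**3. Hand check of the direction (null case, both arms 70%, equal sites, exact balance within site).** The crude analysis uses variance 0.70 × 0.30 = 0.21 per woman. The true variance is 0.21 minus the variance of the site rates.
- SD 0.5: site rates 0.53, 0.63, 0.69, 0.74, 0.78, 0.84 have variance 0.0102. The standard error (SE) is too large by √(0.21/0.1998) = 1.025. The type I error is P(|Z| > 1.96 × 1.025) = 4.4%.
- SD 1.0: site rates 0.38, 0.57, 0.69, 0.78, 0.86, 0.93 have variance 0.0340. The ratio is √(0.21/0.1760) = 1.092, and the type I error is 3.2%.

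**4. Simulation, balanced within site.** 100,000 trials per setting, 121 per arm, 85% vs 70%, six near-equal sites; Pearson chi-square against Cochran-Mantel-Haenszel (CMH).

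| Site-logit SD | Power, unadjusted | Power, CMH | Type I error, unadjusted |
|---|---|---|---|
| 0 | 80.9% | 80.6% | 5.0% |
| 0.25 | 81.1% | 81.1% | 4.8% |
| 0.5 | 81.4% | 82.3% | 4.4% |
| 0.75 | 82.0% | 83.9% | 3.8% |
| 1.0 | 82.6% | 86.0% | 3.2% |

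The stratified test stays at about 5.0% throughout. The simulated type I errors at SD 0.5 and 1.0 agree with step 3. Under 85% vs 70%, the crude SE of the risk difference against its true SD is 0.0525 vs 0.0516 at SD 0.5 (about 2% too wide) and 0.0526 vs 0.0488 at SD 1.0 (about 8%). Coverage of the crude 95% interval is 94.7%, 95.2% and 96.4% at SD 0, 0.5 and 1.0.

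**5. Unequal sites** (60/20/15/10/8/8 per arm, one arrangement only). At SD 1.0 power is 82.2% vs 84.1%, a gain of 1.9 points, the largest in this set.

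**6. Simple randomisation within site.** The unadjusted test keeps its level (4.95% to 4.96%) and the crude SE is right. Power, unadjusted vs CMH: 80.4% vs 79.5% at SD 0, 80.5% vs 81.2% at SD 0.5, 80.5% vs 85.0% at SD 1.0.

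**7. Other denominator.** Suppose all 142 per arm are analysed and women who do not conceive count as having no live birth. The rates become 0.90 × 70% = 63.0% and 0.90 × 85% = 76.5%. With 200,000 trials per setting and near-equal balanced sites, power, unadjusted vs CMH, is 70.2% vs 70.2% (SD 0), 70.4% vs 71.0% (0.3), 70.5% vs 72.4% (0.5) and 71.1% vs 75.2% (0.8). Unadjusted type I error is 4.5% at SD 0.5 and 3.7% at SD 0.8. The gain from stratifying is of the same order as in step 4.

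None of these runs includes the age and previous-miscarriage adjustment.

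**The case against.** The strongest reply is that the effect may be nil. It needs hospitals that differ, and the article gives no evidence of how much six tertiary university-affiliated hospitals would. A 4-point loss needs a very wide spread of live-birth rates. The excess width also needs close balance within hospital; ordered opaque envelopes and stratification are described, but no blocks. The error is in the safe direction, and a full analysis plan could add site. All of this stands, and it limits the size and the severity. It does not remove the mismatch, because the article states a specific covariate list without site.

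Three stronger readings are tempting and are not supported:
- **That the intervals are certainly too wide.** This holds only under the two conditions above. With no site differences nothing is lost.
- **That omitting site takes the trial below its planned power.** At 121 per arm and 85% vs 70%, the unadjusted test stays at or above 80% in every scenario, so the loss is relative to a better analysis. The roughly 70% in step 7 comes from counting women who do not conceive in the denominator, which is a separate question and adds no weight here.
- **That no analysis decides the trial.** The article has groups compared by the named tests and has differences and relative risks described, so a fair reading is that the test decides. Naming the deciding model is commonly left to an analysis plan, and an unadjusted difference beside an adjusted relative risk is not in itself an error.

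**Conclusion.** The point holds as a minor one. Randomisation is stratified by site, and the stated tests and covariates leave site out.

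With near-equal sites balanced by arm, the loss is about 0 to 2 points of power for a site-logit SD up to 0.5, and about 3 to 4 points at 0.8 to 1.0. It is at most about 2 points with the unequal sites tried. Under simple randomisation within site the unadjusted analysis is valid, and the gain forgone is 0.7 points at SD 0.5 and 4.5 points at SD 1.0. Type I error is not inflated in any scenario.

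The direction is firm where sites differ. The size rests wholly on the assumed between-site variation.

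**What to change.** Use one of two forms for the primary comparison:
- a site-stratified CMH test with Mantel-Haenszel risk difference and relative risk; or
- site added to age and number of previous miscarriages in the relative-risk model, with the risk difference derived under the same adjustment.

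State in advance how small sites will be pooled. Keep the unadjusted chi-square as a supportive result.

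The cost is wording only, with no new data. If sites do not differ, stratifying costs about 0.3 points of power or less with arms balanced within site, and about 0.8 points (80.4% vs 79.5%, before rounding 80.37% vs 79.54%) under simple randomisation. For sparse secondary outcomes site may have to be pooled or dropped, and the plan should say so beforehand. This is a free improvement of minor severity, best settled before any outcome is seen by arm.

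### The primary comparison gets a covariate-free test and a covariate-adjusted relative risk, and the plan does not say which decides; one adjusted analysis supplying all three results would settle it at no cost.

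*Protocol article*

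**What the plan says.** The Data analysis section of the Protocol article defines the primary analysis as a comparison of live birth rates between the prednisone, HCQ and anticoagulant arm and the anticoagulant-only arm. Three statements then bear on how it is done.

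- The test: "Comparison between groups will be performed using the independent sample" t test, Pearson's chi-square test or Fisher's exact test, as appropriate. For a binary outcome this leaves chi-square or Fisher, and neither takes covariates.
- The effect measures: "The absolute differences and relative risks with 95% confidence intervals will be described for the primary and secondary outcomes".
- The adjustment: "The relative risks will be adjusted for age and number of previous miscarriages". No adjustment is stated for the absolute differences.

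The same section sets the significance level: "Two-tailed significance tests will be performed at the 5% significance level, without adjustment for multiple testing". The Randomization and blinding section says allocation is "with a ratio of 1:1:1 stratified by site". Site appears neither in the tests nor among the adjustment variables.

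**The concern.** One outcome and one contrast are given two analyses that condition on different things. As written, the p-value ignores age and number of previous miscarriages, the relative risk uses them, and the risk difference has no adjustment stated. The plan names a single primary endpoint, which fixes the outcome and the contrast but not which result carries the conclusion.

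If the test gives p just above 0.05 while the adjusted interval for the relative risk excludes 1, or the reverse, the text offers no rule. The report would then show a p-value and an interval that disagree about the trial's only primary comparison. The plan already treats both covariates as worth adjusting for, so the inconsistency can be removed without collecting or assuming anything new.

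**Working it through.** **1. The plan's own figure.** Inputs from the Sample size section: live birth "is 85% vs 70% for anticoagulant only", "with a power of 0.8 at a two-sided" 5% level, and "We need to enroll 363 women (121 in each group and for the third arm as well").

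Formula for two proportions, pooled variance under the null, no continuity correction:

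n = [z(0.975)·√(2·p̄·q̄) + z(0.80)·√(p1·q1 + p2·q2)]² / (p1 − p2)²

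- p̄ = (0.85 + 0.70)/2 = 0.775, so 2·p̄·q̄ = 2 × 0.775 × 0.225 = 0.34875, root 0.5906
- p1·q1 + p2·q2 = 0.1275 + 0.2100 = 0.3375, root 0.5809
- n = (1.960 × 0.5906 + 0.8416 × 0.5809)² / 0.15² = 2.711/0.0225 = 120.5, rounded up to 121

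Power at 121 per group is 0.802. Inflation: 121/(0.90 × 0.95) = 141.5, so 142 per group and 3 × 142 = 426. The stated figures reproduce. The sizing is for an unadjusted comparison, and the unadjusted test achieves it.

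**2. Unadjusted test against an adjusted relative risk.** The document gives no prognostic strength for age or previous losses, so a range is assumed: odds ratio for live birth per SD of age, and for three or more losses against two, with half the women in each loss group. Each row is 3,000 simulated trials at 121 per group, 85% against 70%. The adjusted analysis is a modified Poisson model with robust variance.

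| Assumed strength (OR per SD age; OR ≥3 losses) | Power, chi-square | Power, adjusted RR | Change (points) | Disagree at 5% |
|---|---|---|---|---|
| None (1; 1) | 79.7% | 78.7% | -1.0 | 1.9% |
| Weak (0.8; 0.7) | 80.9% | 80.5% | -0.4 | 3.7% |
| Moderate (0.67; 0.5) | 80.5% | 81.3% | +0.8 | 4.8% |
| Strong (0.5; 0.4) | 79.9% | 82.7% | +2.8 | 7.7% |

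The Monte Carlo standard error of each paired change is at most about √(disagreement/3,000): 0.25 points in the first row and 0.5 points in the last.

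**3. Unadjusted test against a standardised logistic model**, again at 121 per group and 85% against 70%, over four assumed strengths from none to strong: power changes of 0, +1.1, +2.0 and +3.6 points, with disagreement on significance in 2.0% to 6.3% of trials.

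**4. Type I error.** With 70% in both arms, the chi-square test rejects in 4.7% to 5.3% of trials and the adjusted relative risk in 4.7% to 5.3% (standard error about 0.4 points). The standardised logistic test rejects in 4.8% to 5.8%. The two analyses in step 2 disagree in 0.7% to 3.4% of null trials.

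**5. All randomised women.** If all 142 per group are analysed and women who do not conceive count as having no live birth (an assumption), the rates are 0.90 × 85% = 76.5% and 0.90 × 70% = 63%. Under the same four strengths and the modified Poisson model, disagreement is 2.3% to 9.3% and the power change is -0.6 to +4.2 points.

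None of these simulations includes a site effect.

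**The case against.** **The text has a natural reading.** Groups are compared by tests and effect measures are described, so the test decides; this also matches the basis of the sample size. The reading is reasonable and may be what was meant. It is not conclusive, because the list of tests is generic, covers every outcome and names none for the primary comparison.

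**This is detail for the analysis plan.** If the article had merely left out the model, that would be fair and there would be no point to make. Here it commits to two different analyses of one comparison without ranking them, and an analysis plan that followed the wording would inherit the mismatch. Blinding of the data analysts lowers the risk of a results-driven choice but does not say which result prevails.

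**Disagreement between two valid analyses near the threshold is unremarkable.** True. It occurs in 1.9% of trials even when the covariates have no effect. It needs a stated rule and does not show that either analysis is wrong.

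Three stronger readings are tempting, and the documents support none of them.

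- *The plan gives power away.* The stated 80% is for the unadjusted test and is met. Any gain from adjustment depends wholly on assumed prognostic strength, and with the modified Poisson relative risk the change is slightly negative when the covariates are weak or unrelated to outcome.
- *The unadjusted interval is too wide.* Randomisation was stratified by site, not by age or previous losses. Leaving those two out therefore costs some precision at most, and the interval remains valid.
- *Type I error is inflated.* From step 4, the chance that at least one analysis is significant under the null is (P(first) + P(second) + P(disagree))/2, for example (5.3 + 4.7 + 3.4)/2 = 6.7% at the strong setting. That matters only if success may be claimed on either result, a rule the plan never states.

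**Conclusion.** The point holds as an unresolved mismatch. The test of live birth is covariate-free, no adjustment is stated for the risk difference, the relative risk is adjusted for two covariates, and the decisive result is not named. Under assumed prognostic strengths, test and adjusted analysis land on opposite sides of 5% in about 2% to 8% of trials at 121 per group. Moving to an adjusted test changes power by about 0 to +4 points with the standardised logistic model, or -1 to +3 points with a modified Poisson relative risk. These ranges rest on the planned rates of 85% and 70% and on covariate effects that the document does not quantify.

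The planned test is not invalid and the trial is not underpowered on this account. This is a free improvement: it removes an ambiguity and may add a little power.

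**What to change.** Name one primary analysis in the protocol or analysis plan, before treatment codes are released:

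- a logistic model for live birth with arm, age, number of previous miscarriages and site, the stratification factor;
- p-value, risk difference and relative risk for the primary contrast all taken from that model by marginal standardisation, with the variance method stated;
- the chi-square test kept as a labelled unadjusted sensitivity check, with a sentence saying that it does not decide.

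Fix in advance how age and number of losses enter the model and how small sites are merged. At the planned rates, 121 × 0.30 + 121 × 0.15 is about 54 women without a live birth, or about 9 per site if the six sites recruit evenly, so a sparse site is possible.

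The cost is wording. Age and obstetric history are already recorded at screening, site is known from randomisation, and the sample size need not change. Logistic standardisation is one of several sound choices; what matters is that one model is named and that all three results come from it.

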### Trial management

A steering committee comprised of a local principal investigator at each participating hospital will manage the trial. Screening and recruitment will be reviewed regularly at steering committee meetings; protocol deviations (e.g., late administration) will be distinguished from protocol violations (e.g., missed doses). Enrollment or adherence barriers will be addressed by implementing improvement strategies. Relevant clinical and laboratory data submitted to the steering committee will be checked for completeness and accuracy. All investigators will undertake a standardized training for study procedures, data collection, and adverse event reporting. The plans to promote participant retention and complete follow-up include giving a specific follow-up schedule and obtaining at least two phone contacts to ensure communication. The research assistant will contact participants by telephone regularly to improve adherence to medication and assessments. We will record and analyze reasons for nonadherence or nonretention in the study. To maintain confidentiality, CRFs and other records will be identified by a coded number and initials only. Data tools and instruments are stored securely, and access is restricted to authorized study team members.

### Safety monitoring

An independent data and safety monitoring board (DSMB) will meet regularly to ensure patient safety and data quality. Interim analyses of principal safety and effectiveness outcomes will be performed on behalf of DSMB by the trial statistician who is blind to the treatment assignments. Vital signs, which include blood pressure, heart rate, temperature, and respiration rate, adverse events will be monitored regularly throughout the trial. Safety monitoring and surveillance will be collected, processed, reviewed, evaluated, reported, and discussed, including clinical pregnancy outcomes, identified risks of drugs (Additional file 2), laboratory abnormalities, and imaging changes. If serious adverse outcomes or rare possible risks occur, a multidisciplinary safety management team (SMT) will be established in each participating hospital, and the results will be communicated with DSMB. After assessing severity and causality, rheumatologists are responsible for adjusting further treatment plans accordingly, and adverse events will be communicated with DSMB as soon as possible.

